## *Subject Withdrawal Criteria*

Subjects may be withdrawn from the study if any one or more of the following events occur:

- The subject wishes to withdraw from the study without providing any explanation
- Subject is lost to follow-up
- Refusal of the subject to continue treatment and/or follow-up observations
- Serious adverse event
- Significant protocol deviation/violation or noncompliance, either on the part of the subject or investigator
- Any decision made by the investigator or sponsor that termination is in the subject’s best medical interest
- Device failure or impossibility to continue surgical circumcision for any reason
- Other ethical or clinical considerations upon investigator discretion.

**NOTE: The subject must know in advance that if the subject wishes to withdraw from the study, he must undergo surgical circumcision immediately upon removal of the device.**

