## 4.1Source of Subjects and Enrollment

Male subjects that are voluntary scheduled for circumcision. Only subjects who have signed the last version of an Independent Ethical Committee (IEC)/Institutional Review Board (IRB) approved Informed Consent Form (ICF) and meet all of the eligibility criteria listed below will be qualified for enrollment. The study will recruit at least 100 evaluable subjects who will complete the protocol procedure /treatment and the follow-up schedule.

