## *Handling of Withdrawals*

In accordance with the current revision of the Declaration of Helsinki and local Authority regulations at the corresponding countries, a subject has the right to withdraw from the study at any time, for any reason, without prejudice to his future medical care by the physician or the institution. The investigator and the sponsor also have the right to withdraw subjects from the study in the event of serious adverse events, protocol departure, or other reasons. Should a subject (or the subject’s legally authorized representative) decide to withdraw, all efforts will be made to collect and report the final visit observations, and the reasons for withdrawal, as thoroughly and timely as possible.

Withdrawals will be recorded, analyzed and reported to the local Ethical Committee.

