8. STUDY DESIGN

## 8.1 Study Design

Assessing Odor Level when Using PrePex for HIV Prevention: A Prospective, Randomized, Open Label, Blinded Assessor Trial to Improve Uptake of Male Circumcision.

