## 8.2 Sample Size

One hundred (100) subjects scheduled for voluntary circumcision. The subjects will be randomly divided into three balanced study arms: Arm 1, Arm 2 and Arm 3 which will include thirty three (33) subjects respectively.

**Arm 1:** A control arm – subjects instructed to follow the current hygiene instructions of standard washing with soap and water during a daily shower. They will get a soap to take home and will be questioned daily to make sure they followed the cleaning instructions.

They might be requested to wash themselves at the hospital before the actual Removal visit starts.

**Arm 2:** subjects instructed to clean the foreskin with soapy water once a day using a syringe.

They will get a soap and required accessories to take back home and will be questioned daily to make sure they followed the instructions.

Subjects may be requested to wash themselves at the hospital before the actual Removal visit starts.

**Arm 3:** subjects instructed to clean the foreskin with diluted chlorhexidine (1%) once a day using a syringe. They will get chlorhexidine in tubes and required accessories to take back home and will be questioned daily to make sure they followed the instructions.

Subjects may be requested to wash themselves at the hospital before the actual Removal visit starts.

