## 8.3.1 General Considerations

The primary analysis will be performed on an intent-to-treat basis. Per-protocol analysis also will be performed as a secondary analysis. The required significance level of findings will be equal to or lower than 5%. All statistical tests will be two-sided. Where confidence limits are appropriate, the confidence level will be 95%.

All data will be presented via descriptive statistics. Binary data such as adverse events success/fail criteria will be presented as a count and percentage together with an exact 95% confidence interval. Adverse event rates will be compared descriptively with the reported rates of similar treatments. Continuous data will be represented by a mean, standard deviation, median, minimum and maximum together with 95% confidence intervals for the means.

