**8.3.2.1 Intent-to-Treat Population**

The intent-to-treat (ITT) population will include all patients enrolled in arms 1,2 or 3 of the study. This population will include all subjects from visit 1 that were placed with the device.

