# 16. Removal of Subjects from the Study

A subject has the right to withdraw from the study at any time, for any reason, without prejudice his future medical care by the physician or the institution. Should a subject decide to withdraw, all efforts will be made to collect and report the final visit observations as thoroughly and timely as possible. **However,** **subject should know that if the subject wishes to withdraw, he will need to undergo surgical circumcision.**

Subjects may be removed from the study if any one or more of the following events occur:

- Refusal of the subject to continue treatment and/or observations;
- Decision by the Investigator that termination is in the subject’s best medical interest;
- Subject is lost to follow-up;
- Other ethical or clinical considerations.

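### Staff may withdraw a man for significant noncompliance, which can include not following the randomised cleaning, and nothing secures his remaining smell tests, so the intent-to-treat odor comparison could drift towards compliers

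*Protocol*

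**What the plan says.** Two places in Section 4 of the protocol let staff end a man's participation for not following the plan. The Subject Withdrawal Criteria state that subjects may be withdrawn for, among other things, "Significant protocol deviation/violation or noncompliance, either on the part of the subject or investigator". Handling of Withdrawals adds: "The investigator and the sponsor also have the right to withdraw subjects from the study in the event of serious adverse events, protocol departure", or for other reasons. Neither defines significant, and neither names the cleaning routine.

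The cleaning routine is what is randomised (Section 8.2): daily shower in Arm 1, soapy water by syringe in Arm 2, diluted chlorhexidine by syringe in Arm 3. In every arm compliance is checked each day; subjects "will be questioned daily to make sure they followed the instructions". Only the odor assessors are blinded. Section 8.1 calls the study "A Prospective, Randomized, Open Label, Blinded Assessor Trial to Improve Uptake of Male Circumcision".

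On analysis, Section 8.3.1 says: "The primary analysis will be performed on an intent-to-treat basis". Section 8.3.2.1 defines that population by device placement: "This population will include all subjects from visit 1 that were placed with the device". Section 8.3.2.2 defines a separate per-protocol set without major violators. Section 4.1 sets the target: "The study will recruit at least 100 evaluable subjects who will complete the protocol procedure /treatment and the follow-up schedule".

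Section 16 gives another permissive list, opening "Subjects may be removed from the study if any one or more of the following events occur", which does not mention noncompliance. Handling of Withdrawals and Section 16 ask for efforts to collect final-visit observations, but word this for a subject who himself decides to withdraw.

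**The concern.** When the treatment is an instruction to clean at home, failing to do it is part of what the instruction achieves. An intent-to-treat comparison is meant to include that failure. Here, people who know both the arm and the daily compliance answers hold a discretionary power to take a man out before his Day 7 odor is measured. He still counts as a member of the intent-to-treat population, but he has no Day 7 value, and the hypothesis in Section 1 concerns odor just before removal on Day 7.

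The trial's stated purpose (Section 3) is a cleaning guideline for the routine program. If men who do not manage a routine are selectively unmeasured, the result describes those who manage it and not those who are told to use it.

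**Working it through.** **Inputs.** Effect size 0.7 SD, 80% power, 5% level and 33 per arm (Section 8.3); two-sided tests (Section 8.3.1). The documents give no noncompliance or withdrawal rate, so those below are assumptions.

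**1. The plan's own figure.** n per group = 2 × (1.960 + 0.842)² / 0.7² = 2 × 7.849 / 0.49 = 32.04, rounded up to 33. The exact t calculation gives 33.02, with power 79.97% at 33. The stated 33 is reproduced and is not in dispute.

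**2. Upper-bound illustration with a real effect.** Let a fraction f of a syringe arm not comply and smell like control, and let all control subjects comply. The as-assigned effect is 0.7 × (1 − f). If every noncomplier is withdrawn and none has a Day 7 value, the comparison estimates 0.7. The ratio of the two is 1/(1 − f).

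| Assumed f | As-assigned effect (SD) | After withdrawal (SD) | Overstatement | Left of 33 |
|---|---|---|---|---|
| 10% | 0.7 × 0.9 = 0.63 | 0.70 | 1/0.9 = 1.11, 11% | 29.7 |
| 20% | 0.7 × 0.8 = 0.56 | 0.70 | 1/0.8 = 1.25, 25% | 26.4 |
| 30% | 0.7 × 0.7 = 0.49 | 0.70 | 1/0.7 = 1.43, 43% | 23.1 |

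**3. What control withdrawals do to this.** Let a fraction c of control also fail to wash and smell g SD worse than washing controls. The as-assigned effect becomes 0.7 × (1 − f) + g × c. Withdrawing all noncompliers from both arms still leaves 0.7, so the overstatement is 0.7 × f − g × c. It is zero when g × c = 0.7 × f and turns into an understatement beyond that. The direction therefore depends on quantities the protocol does not give.

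**4. No true difference between techniques.** In 40,000 simulated trials per scenario, with 33 per arm and a two-sided t-test at 5%, the poorest cleaners were withdrawn at the rates shown. r is the correlation between poor cleaning and odor.

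| Withdrawn, control / syringe | Type I error, r = 0.3 | r = 0.5 | r = 0.7 |
|---|---|---|---|
| 5% / 10% | 0.051 | 0.054 | 0.057 |
| 5% / 20% | 0.060 | 0.073 | 0.101 |
| 5% / 30% | 0.070 | 0.111 | 0.179 |
| 20% / 20% | 0.051 | 0.049 | 0.049 |

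At 5% / 30% the bias is 0.12, 0.19 and 0.27 SD in favour of the arm that loses more men. With r = 0, or with equal withdrawal, the bias is zero and the error stays at about 0.05. By symmetry, heavier withdrawal from control would favour control.

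**5. Is the missing outcome otherwise protected?** Day 0 readings, and any Day 3 and Day 5 readings before withdrawal, remain. For later readings, the final-visit clause covers subject-initiated withdrawal only. The note under the Subject Withdrawal Criteria, also worded for a man who wishes to withdraw, has surgery follow device removal at once. If it were applied to a staff withdrawal before Day 7, no smell test with the device in place could follow. The protocol does not say whether it applies.

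**The case against.** The strongest reply is that this is ordinary withdrawal wording. It says may, requires significant noncompliance, covers the investigator's conduct as well, and nowhere says that a missed wash leads to withdrawal. The intent-to-treat definition has no compliance exclusion. Missing Day 7 values are commonly handled in a statistical analysis plan, which is not at hand. Withdrawals must be recorded, analysed and reported to the ethics committee, so an imbalance could be noticed. The device is worn for only seven days, and the protocol's hypothesis is about men who do follow a washing technique.

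Most of this stands, and it limits the point. A reader might infer that the primary comparison becomes compliers-only. That would need every noncomplier to be withdrawn, which no text says. A reader might also infer that the bias favours the syringe arms because irrigation is harder to keep up than a shower. The protocol makes no such statement and gives no compliance rate for any arm, and Arm 1 men are questioned daily under the same rule. Nor do Section 4 and Section 16 strictly contradict each other: both lists are permissive, and Section 16 also leaves out serious adverse events and device failure and ends with an open clause.

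What the reply does not meet is the data-collection gap. An analysis plan can define populations and impute, but it cannot recover a smell test that was never done. The adherence-type hypothesis does not remove the gap either, since the protocol names intent-to-treat as primary and already has a per-protocol set for the other question.

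**Conclusion.** The point holds as a possibility that the protocol leaves open. Unblinded staff can withdraw men for not following the randomised routine, no text keeps those men in the remaining smell tests, and the intent-to-treat odor comparison could drift towards compliers as a result. Bias between arms needs two further conditions: more poor cleaners withdrawn from one arm, and worse odor in those men. The second is close to the protocol's own hypothesis; the first is unknown.

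The 11-43% is an upper bound for assumed noncompliance of 10-30%. It rests on all syringe-arm noncompliers smelling like control, all being withdrawn without a Day 7 value, and none being withdrawn from control. It is not an expected overstatement, and the direction is not established. This is a cheap improvement worth making before enrolment and ranks below a must-fix.

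**What to change.** In both the Subject Withdrawal Criteria and Handling of Withdrawals, state that not following the assigned cleaning is not by itself a ground for withdrawal from the study. Changing only the first list would leave the same route open through the protocol-departure clause. Align Section 16 with that wording. Add that such subjects keep every scheduled smell test while the device is in place and are analysed in their randomised arm, and that noncompliance is used only to define the per-protocol set. Safety-based and subject-initiated withdrawal stay as written.

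The cost is protocol wording, since the Day 3, 5 and 7 visits are already scheduled. The downside is a possibly smaller observed difference. Under the assumptions of step 2, power with all 33 per arm kept (normal approximation) would be 0.73, 0.62 and 0.51 at f = 10%, 20% and 30%, against 0.81 with full compliance. Withdrawing the noncompliers would give 0.79, 0.76 and 0.73, but for the full-compliance effect and not for the as-assigned effect that the primary analysis is meant to estimate.

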The procedure will be carried out in a clean non-sterile environment. The subject will undergo sizing of the penis sulcus with the PrePex Sizing Plate. The penis will be cleaned by red Povidone-Iodine solution or other disinfection solution (Chlorahexidine, etc.) with the foreskin stretched backwards to expose the inner skin for the disinfection solution. Then the foreskin will be dried with a dry gauze. The Operator will then mark the circumcision line with a clean skin marker and then the Assistant will open the corresponding sized package of the PrePex device, and will load the Elastic Ring on to the Placement Ring. Then, Lidocaine 5% dermal cream will be applied on the inner foreskin. The Placement Ring with the Elastic Ring will be placed on the penis shaft and the foreskin tip will be stretched open to the sides by the operator hands, the operator may select to use a dry gauze to affirm the grip. Then, the Inner Ring will be applied through the stretched foreskin and over the glans penis (hereinafter, "glans") so that it will be placed fixed over the sulcus behind the glans (the base of the glans). At this point, the foreskin around the inner ring is held tight by the Assistant, and the Placement Ring and Elastic-Ring are approximated to the Inner Ring by the Operator. The foreskin is then adjusted to fit the circumcision marking line to the Elastic-Ring. Then, the Elastic-Ring is released from the Placement Ring on to the Inner Ring groove, initiating homeostasis. The procedure is then completed. Medication based on 400mg Ibuprofen is given to the subject to use at home if needed. The subject will then take part in a formal discharge session in a class room, where he will be instructed to return for a follow up visit and in any non sustained situation and to take painkillers in case of pain. The device will remain in situ for 7 days, at which the subject will return for a removal visit (i.e. if placed on Monday, removed on the following Monday). In case subjects arrive on day 5 or 6 and require removal of the device and foreskin, it is for the medical decision of the center managing physician to perform the removal if he/she thinks the removal is safe at this day. Those subjects will be followed for the procedure safety and efficacy. The foreskin is removed using sterile scissors, the Elastic Ring is removed using a #10 scalpel (surgical blade), and then the Inner Ring is extracted using a spatula or fingers, depending on the thickness of the foreskin. The area might be compressed with gauze for 30 seconds to avoid oozing and clear exudates. Following the removal process, the circumcision area will be dressed with a non-adherent sterile pad for 2 days, the subject will receive one dressing pad for home to change in case the dressing gets wet. The subject will then take part in a formal discharge session in a class room, where he will be instructed to turn to his local health center in any non sustained situation. Following the 2 days (day 9) the subject will remove the dressing on his own at home. The subject will be instructed to return in any non sustained situation, regardless of the follow-up visit.

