## 6.2 Informed Consent Procedure

- - In obtaining and documenting informed consent, the investigator should comply with the applicable regulatory requirements, and should adhere to GCP, HIPAA and the ethical principles that have their origin in the Declaration of Helsinki
  - Prior to the beginning of the trial, the investigator should have the written informed consent form and any other written information approved by the National Ethical Committee before it is provided to subjects
  - The written informed consent form and any other written information to be provided to subjects should be revised whenever important new information becomes available that may be relevant to the subject’s consent. Any revised written informed consent form, and written information must be approved by the Ethic Committee before it is made available for subject signature. The subject should be informed in a timely manner if new information becomes available that may be relevant to the subject’s willingness to continue participation in the trial. The communication of this information should be documented
  - Neither the investigator, nor the trial staff, should coerce or unduly influence the subject to participate or to continue to participate in a trial. He will also testify of his agreement by a signature on the same ICF
  - The investigator, or a person designated by the investigator, should fully inform the subject of all pertinent aspects of the trial including the Ethical committee approved written informed consent
  - Before informed consent may be obtained, the investigator, or a person designated by the investigator, should provide the subject ample time and opportunity to inquire about details of the trial and to decide whether or not to participate in the trial. All questions about the trial should be answered to the satisfaction of the subject
  - Prior to a subject’s participation in the trial, the Ethical Committee approved written informed consent form should be signed and personally dated by the subject or by the subject's legally acceptable representative, and by the person who is authorized to conduct the informed consent discussion
  - Prior to participation in the trial, the subject should receive a copy of the signed and dated written informed consent form and any other written information provided to the subjects.

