**Procedure:**

After assessment of eligibility and after the subject has signed the informed consent form, the subject will be enrolled in the study.

A **standard PrePex procedure** is described below:

The procedure will be carried out in a clean non-sterile environment. The subject will undergo sizing of the penis sulcus with the PrePex Sizing Plate. The penis will be cleaned by red Povidone-Iodine solution or other disinfection solution (Chlorahexidine, etc.) with the foreskin stretched backwards to expose the inner skin for the disinfection solution. Then the foreskin will be dried with a dry gauze. The Operator will then mark the circumcision line with a clean skin marker and then the Assistant will open the corresponding sized package of the PrePex device, and will load the Elastic Ring on to the Placement Ring. Then, Lidocaine 5% dermal cream will be applied on the inner foreskin. The Placement Ring with the Elastic Ring will be placed on the penis shaft and the foreskin tip will be stretched open to the sides by the operator hands, the operator may select to use a dry gauze to affirm the grip. Then, the Inner Ring will be applied through the stretched foreskin and over the glans penis (hereinafter, "glans") so that it will be placed fixed over the sulcus behind the glans (the base of the glans). At this point, the foreskin around the inner ring is held tight by the Assistant, and the Placement Ring and Elastic-Ring are approximated to the Inner Ring by the Operator. The foreskin is then adjusted to fit the circumcision marking line to the Elastic-Ring. Then, the Elastic-Ring is released from the Placement Ring on to the Inner Ring groove, initiating homeostasis. The procedure is then completed. Medication based on 400mg Ibuprofen is given to the subject to use at home if needed. The subject will then take part in a formal discharge session in a class room, where he will be instructed to return for a follow up visit and in any non sustained situation and to take painkillers in case of pain. The device will remain in situ for 7 days, at which the subject will return for a removal visit (i.e. if placed on Monday, removed on the following Monday). In case subjects arrive on day 5 or 6 and require removal of the device and foreskin, it is for the medical decision of the center managing physician to perform the removal if he/she thinks the removal is safe at this day. Those subjects will be followed for the procedure safety and efficacy. The foreskin is removed using sterile scissors, the Elastic Ring is removed using a #10 scalpel (surgical blade), and then the Inner Ring is extracted using a spatula or fingers, depending on the thickness of the foreskin. The area might be compressed with gauze for 30 seconds to avoid oozing and clear exudates. Following the removal process, the circumcision area will be dressed with a non-adherent sterile pad for 2 days, the subject will receive one dressing pad for home to change in case the dressing gets wet. The subject will then take part in a formal discharge session in a class room, where he will be instructed to turn to his local health center in any non sustained situation. Following the 2 days (day 9) the subject will remove the dressing on his own at home. The subject will be instructed to return in any non sustained situation, regardless of the follow-up visit.

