**PrePex MC**

**Classification of Adverse Events and Device Hazards**

| **Adverse**  **Event** | **Description** | **Severity** | **Code** |
| --- | --- | --- | --- |
| **A. During Placement** | | | |
| Pain | Pain score of 8 or more not requiring anesthesia  Requires anesthesia  Not controlled by additional anesthesia | Mild  Moderate  Severe | APP1  APP2  APP3 |
| Difficulty in applying the device | Could not apply device; determined as contra indicated; no harm to tissue or subject  Had to push unusually hard, but no harm to tissue or subject and no change to procedure  The device cut through the foreskin, with or without minor bleeding, No change in procedure  The device cut through the foreskin, with or without minor bleeding, and requiring a change to surgical method  The device cut through the foreskin, causing significant bleeding and requiring a change to surgical method | No AE  No AE  Mild  Moderate  Severe | --  --  ADD1  ADD2  ADD3 |

| **Adverse**  **Event** | **Description** | **Severity** | **Code** |
| --- | --- | --- | --- |
| **B. While Wearing the Device** | | | |
| Pain / Discomfort | Not requiring intervention beyond painkiller or anesthetic cream  Requiring early device removal by PrePex Operator or by client  Requiring early device removal and anesthesia  Not controlled by device removal or additional anesthesia | Not AE  Mild  Moderate  Severe | --  BWP1  BWP2  BWP3 |
| Device displacement / spontaneous detachment | Device displacement with no clinical consequences  Complete spontaneous detachment, or patient removed device himself with no adverse clinical consequences  Device displacement requiring re-placement  Device displacement requiring surgical intervention  Displacement or detachment and penile damage present | Not AE  Mild  Moderate  Severe | --  BDD1  BDD2  BDD3 |
| Early device removal (i.e. 4 days or less with the device) | Device removed due to pain, swelling or bleeding  Device removed due to pain, swelling or bleeding requiring surgical intervention  Device removed and penile damage present | Mild  Moderate  Severe | BER1  BER2  BER3 |
| Edema | More edema than usual but not causing any discomfort to the patient  Moderate edema causing the patient discomfort, though managed with conservative measures  Severe edema, causing the patient discomfort, uncontrolled with conservative measures | Mild  Moderate  Severe | BED1  BED2  BED3 |

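### The protocol has men told that withdrawing means surgical circumcision, which ties surgery to the choice to withdraw and not to early device removal, clinical need and consent

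*Protocol*

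**What the plan says.** Two places state what follows from withdrawal, and both frame it as something the man is to know.

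- The note closing the Subject Withdrawal Criteria (section 4) says that "if the subject wishes to withdraw from the study, he must undergo surgical circumcision immediately upon removal of the device".
- Section 16, Removal of Subjects from the Study, says that the "subject should know that if the subject wishes to withdraw, he will need to undergo surgical circumcision".

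The general rules on withdrawal and consent are unconditional. Handling of Withdrawals says that "a subject has the right to withdraw from the study at any time, for any reason, without prejudice to his future medical care", and section 16 gives the same right just before its surgical statement. Section 6.2 says: "Neither the investigator, nor the trial staff, should coerce or unduly influence the subject to participate or to continue to participate in a trial".

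The appended classification of adverse events, part B (while wearing the device), treats surgery after early removal as a separate, higher grade: "Device removed due to pain, swelling or bleeding requiring surgical intervention" is Moderate. Removal for the same reasons with no surgery mentioned is Mild.

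**The concern.** A warning about stopping mid-course is reasonable. The Clinical background explains that the device cuts off blood flow to the distal foreskin, which becomes necrotic, so taking the device off early can leave tissue that needs surgical completion. Such a warning would depend on two facts: that the device came off early, and what state the tissue was in.

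The text depends on neither. It makes surgery follow from the man's wish to leave the study, although leaving the study and removing the device are different events. A man may want to stop the smell tests, the photographs or the partner interview and still keep the device until routine removal. A serious adverse event or a device failure may take the device off early with no wish to withdraw, and the note says nothing about surgery there.

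What is at stake is voluntariness. A man told in advance that withdrawing means an operation has a reason to stay that is unrelated to his clinical need.

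**Working it through.** There is no figure to reproduce and no arithmetic applies. The check sets the texts side by side.

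**1. The two statements**

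| Element | Subject Withdrawal Criteria, note | Section 16 |
|---|---|---|
| Trigger | Wish to withdraw | Wish to withdraw |
| Force | Must | Will need to |
| Refers to device removal | Yes | No |
| Clinical indication required | No | No |
| Consent to surgery required | No | No |
| Framed as advance information | Yes | Yes |

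Nothing elsewhere in the protocol text at hand supplies the missing conditions.

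**2. Before placement.** The Schedule of Events puts consent and randomization at visit 1 (Day -7 to D0) and device application at visit 2 (D0). A man can therefore be consented and randomized with no device on. The intent-to-treat definition in section 8.3.2.1 is limited to men in whom the device was placed, which is consistent with some never reaching placement. Such a man has no ischaemic tissue and no clinical reason for surgery. The section 4 note does not reach him, because it is timed to device removal. Section 16 does, taken as written.

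**3. Device in place, removed early.** Two rows of part B of the adverse event classification are clear:

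- Early device removal (4 days or less): removal for pain, swelling or bleeding is Mild; the same removal requiring surgical intervention is Moderate.
- Pain or discomfort: early removal by the operator or by the client is Mild, and removal that also needs anesthesia is Moderate.

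A third row, on displacement and detachment, includes a man removing the device himself without adverse clinical consequences. In the text at hand this row has five descriptions against four grades (Not AE, Mild, Moderate, Severe). Self-removal is the second description. If the grades run in order and each is used, it is Not AE or Mild, so Mild at most.

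The classification therefore recognises early removal, including by the man himself, that ends without surgery. A statement that withdrawal always entails surgery does not match it.

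**4. Against the consent rules.** Section 16 grants withdrawal without prejudice and then qualifies it with the surgical statement, which names no clinical condition. Section 6.2 bars undue influence to continue. An unconditional operation announced as the consequence of leaving is hard to square with either.

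**The case against.** The strongest reply is that both sentences are duties to inform. Each says what the man is to know; neither orders anyone to operate. That stands. A reader might infer that staff are given a rule to operate without consent. The documents do not support this: nothing lets staff override a refusal, withdrawal without prejudice is preserved, and sections 6.2 and 17 bind the study to GCP.

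Second, the section 4 note presupposes a device in place, and section 16 may be only a shortened repeat of it. That is a fair reading and limits the pre-placement problem to the literal text of section 16. It does not supply a clinical or consent condition in either place.

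Third, every participant wants circumcision (section 4.2), so a warning about surgical completion protects him. The intent is granted. But wanting a device procedure is not consent to an operation, and the warning should depend on early removal.

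Fourth, a reader might contrast the rule with removal on Day 5 or 6, where "it is for the medical decision of the center managing physician to perform the removal". The contrast does not help. Those men need both device and foreskin removed, so the circumcision is finished at that visit, and they remain in follow-up. The absence of a surgical statement there does not show a more lenient rule.

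Fifth, the consent form is not among the material at hand and may already carry the qualification. No claim is made about it.

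**Conclusion.** The point holds as a fault in two statements of the protocol. Both have men told that withdrawing entails surgical circumcision, without a clinical-indication or consent condition, and section 16 also drops the device condition. The trigger should be early removal before circumcision is complete, together with the state of the tissue, and not the man's decision to withdraw.

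Its size is modest. It touches only men who withdraw or consider doing so, and no withdrawal rate is given, so their number cannot be estimated. No sample size, power or error rate changes. Pressure to stay is an inference from the wording; the documents do not show that it occurred.

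The conclusion rests on the protocol text alone and on taking the likely intent to be a safety warning about ischaemic tissue. It should be corrected because it concerns subject protection and conflicts with the protocol's own consent rules.

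**What to change.** Replace the note in the Subject Withdrawal Criteria and the warning in section 16 with one identical text, for example:

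> If the device is removed early, for any reason, before circumcision is complete, surgical completion may be needed; it will be done when the physician judges it clinically indicated and the subject consents. A subject who leaves only the research procedures may keep the device until routine removal, and withdrawal before placement requires no procedure.

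The words on any reason extend the warning to early removal after a serious adverse event, a device failure or an investigator or sponsor decision. Check the consent form for agreement and amend it only if it differs.

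The cost is a wording amendment in two places with ethics committee approval, plus matching consent text if needed. It adds no visits, procedures or subjects and leaves the analysis unchanged.
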